## 13 Case report forms

Novo Nordisk will provide a system for electronic data capture (EDC). This system, and support services to the system, will be supplied by a clinical services vendor, Phase Forward. The activities of this vendor will be under the direction and supervision of Novo Nordisk.

### 13.1 Rules for completing eCRFs

Ensure that all relevant questions are answered and that no empty data blocks exist.

If a test/assessment has not been done and will not be available, or if the question is irrelevant (e.g. is not applicable) indicate this according to the data entry instructions.

The Investigator or Investigator's authorised staff must ensure that all information derived from source documentation is consistent with the source information. By signing the affirmation statement electronically, the Investigator confirms that the information is complete and correct.

### 13.2 Corrections to eCRFs

Corrections to the eCRF data will be made by the Investigator or the Investigator's authorised staff. An audit trail will be maintained in the EDC application containing as a minimum: Identification of the person entering the data, date and time of the entry and reason for the correction.

If corrections are made by the Investigator's authorised staff after the date of the Investigator's signature on the affirmation statement, the statement must be signed again by the Investigator.

### 13.3 eCRF flow

The Investigator must ensure that data is recorded in the eCRFs within 48 hours after the visit. When data is entered it will be available to Novo Nordisk for data verification activities.

Safety laboratory results will be electronically uploaded and must be electronically signed by the Investigator as soon as possible after they have been made available, or not later than 12 hours after being loaded.

Site specific eCRF data (in an electronic readable format) will be provided to the Investigator site after the trial database is released and access to update the trial data on the EDC application is removed. This data will be retained by the site.

When the final clinical trial report is available the data will be archived by Novo Nordisk.

## 14 Monitoring procedures

During the course of the trial, the Monitor will visit the trial site to ensure that the protocol has been adhered to, that all issues have been recorded, to perform source data verification and to monitor drug accountability. The visit intervals will depend on the outcome of the remote monitoring of the eCRFs, the trial site's recruitment rate and the compliance of the trial site to the protocol and GCP. The monitor must at least visit the sites every 8-12 weeks.

The monitor must be given direct access to source documents (original documents, data and records). Direct access includes permission to examine, analyse, verify and reproduce any record(s) and report(s) that are important to evaluation of the clinical trial. In addition the monitor should be available for discussions by telephone. Monitors must perform 100% source data verification of all data points.

Screening failure data must be completed.

The monitor will ensure that the eCRFs are completed.

## 15 Data management

Data management is the responsibility of Data Management, Novo Nordisk Head Quarters. Data management may be delegated under an agreement of transfer of responsibilities to another data management unit within Novo Nordisk or to an external contract research organisation.

The subject and the biological material obtained from the subject will be identified by subject number, trial site and trial identification number. Appropriate measures such as encryption or deletion will be enforced to protect the identity of human subjects in all presentations and publications as required by local/regional/national requirements.

Except for data from gene expression, proteomic profiling of serum/plasma markers, histopathology, and immunohistochemistry analyses, all data from biomarker assessments will be entered into the trial database at least in a processed form. Data from gene expression, proteomic analysis of serum/plasma markers, histopathology, and immunohistochemistry analyses will not be released at the time of trial database release.

Appropriate measures such as encryption of data files will be used to assure confidentiality of subject data when it is transmitted over open networks. In cases where electronic data capture is used, data stored on the Investigator's computer(s) and data during transfer will be secured by encryption.

Laboratory data will be transferred electronically from the central laboratory performing clinical analyses. The electronic laboratory data will be considered source data. In cases where laboratory data is transferred via non-secure electronic networks, data will be encrypted during transfer.

## 16 Evaluability of subjects for analysis

All subjects exposed to trial drug will be included in the safety analysis set used for analysis of safety data. All randomised and exposed subjects will be included in the intention to treat (ITT) analysis set used for the efficacy analysis. The per protocol (PP) analysis set will be comprised of subjects from the ITT analysis set who have fulfilled all inclusion and no exclusion criteria at entry, as well as no withdrawal criteria during trial. The PP analysis of the efficacy data will be viewed as a supportive analysis. The PK/PD analysis set used for the analysis of the PK/PD data will include subjects from the ITT analysis set who have not committed any protocol violations judged to interfere with the pharmacokinetics/pharmacodynamics of 109-0012.

The decision to exclude any subject or observation from statistical analysis is the joint responsibility of the International Trial Manager, Sponsor's Medical Expert and the Statistician. The subjects or observations to be excluded and the reason for their exclusion will be documented and signed by all relevant parties at a review of data prior to database release.

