suggested half-life of about 15-20 days the drug is then anticipated to have been sufficiently cleared from the body.

Other anti-psoriatic treatments, except moisturising cream and low potency corticosteroid cream (group 1), will not be allowed during the trial. For more specific details regarding prohibited concomitant medication see section [6.3](#).

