#### **6.4 Withdrawal criteria**

The subject may withdraw at will at any time.

The subject may be withdrawn from the trial at the discretion of the Investigator or the sponsor due to safety concerns, or if judged non-compliant with trial procedures.

A subject must be withdrawn if the following applies:

1. Non-compliance with protocol procedures
2. Drug limiting toxicity (DLT) or other serious or significant adverse event that warrants discontinuation in the opinion of the investigator
3. Sponsor closure of the trial
4. Withdrawal of informed consent

For the MD dose-escalation phase and the MD expansion phase an **IVRS call** must be performed if the subject is withdrawn.

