#### **Day 57 to Day 148 (± 3 days)**

Subjects will come for regular visits at Day 57, 71, 99, 127 and 148. From Day 57 and onwards a deviation of ± 3 days from the scheduled day will be allowed. The following data and samples will be recorded and collected at each of those visits:

1. Vital signs
2. Haematology
3. Biochemistry
4. Urinalysis
5. Hormones
6. Sampling for serum/plasma biomarkers
7. PK samples
8. Concomitant medication
9. Local tolerability
10. Adverse events

Procedures which are not performed at every visit are listed below together with the time point at which they should be performed:

Day 57 (± 3 days): Lipids, ECG, BSA, PGA, PASI and VAS (if applicable), and quality of life questionnaire. At trial Day 57 all subjects must have been **fasting since midnight the same day** (only water will be allowed from midnight until collection of blood samples).

Day 99 (± 3 days): BSA, PGA, PASI and VAS (if applicable), and sampling for antibodies. Collection of lesional skin biopsies (1x6 mm to be split in half) is optional.

Day 148 (± 3 days): Body measurements (weight only), physical examination, ECG, BSA, PGA, PASI and VAS (if applicable), sampling for antibodies, and quality of life questionnaire.

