### 17.2.2 Secondary endpoints

#### Efficacy:

- PASI (PASI75 is the primary endpoint for the MD expansion phase)
- PGA
- VAS (assessment of arthritis symptoms for subjects with psoriatic arthritis)
- QoL (MD expansion phase only)

PASI75, 75% reduction in PASI, will be assessed by comparing the measurement from the visit at trial Day 29 in the SD phase, and trial Day 57 in the MD phases, to baseline values measured prior to the first dose. PASI90 will be derived analogously.

PASI, PGA and VAS will be listed by trial phase, dose, and time. Additionally, PASI75 and PASI90 will be summarised by trial phase and dose, and PASI, PGA, VAS and QoL will be summarised by treatment group for the MD expansion phase.

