## **18.2 Data handling**

If the subject withdraws the previously given informed consent the subject's data will be handled as follows:

- Data collected will be used as part of the per protocol/intention to treat population.
- Safety events will be reported to International Product Safety, Novo Nordisk /regulatory authorities.

If data is used, it will always be in accordance with local law and subject to IRB/IEC approval.

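### The supportive per-protocol set excludes subjects for events after the PASI75 endpoint visit, and section 18.2 does not agree with section 16 on where consent withdrawals belong

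*Protocol*

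**What the plan says.** Section 16 of the protocol uses the ITT set (randomised and exposed subjects) for the efficacy analysis and treats the PP analysis as supportive. PP members are ITT subjects "who have fulfilled all inclusion and no exclusion criteria at entry, as well as no withdrawal criteria during trial". No visit or day closes that condition.

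Section 6.4 has four criteria under which withdrawal is mandatory: non-compliance with protocol procedures; "Drug limiting toxicity (DLT) or other serious or significant adverse event that warrants discontinuation in the opinion of the investigator"; "Sponsor closure of the trial"; and "Withdrawal of informed consent".

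Section 17.2.2 derives PASI75 by comparing "trial Day 29 in the SD phase, and trial Day 57 in the MD phases, to baseline values measured prior to the first dose". In both MD phases follow-up continues well beyond that (sections 8.1.2 and 8.1.3): "Subjects will come for regular visits at Day 57, 71, 99, 127 and 148".

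Section 18.2 says of a subject who withdraws consent: "Data collected will be used as part of the per protocol/intention to treat population".

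Section 5.3 restricts other therapy throughout: "Other anti-psoriatic treatments, except moisturising cream and low potency corticosteroid cream (group 1), will not be allowed during the trial".

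**The concern.** A PP set is meant to show the treatment comparison in subjects who followed the plan up to the outcome. Here membership also depends on what happens after the outcome has been recorded. Someone who received all four doses, had a valid Day 57 PASI and withdrew consent on Day 100 is dropped from the PP analysis of PASI75, although nothing about that subject's adherence or outcome at Day 57 has changed.

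The later event may also be related to response. Dosing ends at Day 43 and other anti-psoriatic treatment stays barred, so a subject whose disease is uncontrolled has a reason to leave during follow-up. That is an inference, because the protocol gives no withdrawal data. If it is right, the PP response rate rises in whichever arm loses more of its non-responders.

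Sponsor closure is an administrative event. Read literally, an early stop would remove every subject still in follow-up from the PP set, including those with complete endpoint data.

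Separately, sections 16 and 18.2 give different answers for the same subject.

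What is at stake is how the supportive analysis can be read. With 26 and 13 subjects, a few exclusions can move it noticeably.

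**Working it through.** **The plan's own figure.** The PP analysis has none. The nearest is the 83% power in section 17.1 (60% v 10% PASI75, 26+13 subjects, Fisher's exact test). Enumerating all binomial outcomes gives 83.8% with 2.5% in the relevant tail, which agrees with the stated value; the usual two-sided Fisher p-value gives 89.0%. Nothing in this point changes the sample size.

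**Step 1: the exclusion window.**
- Endpoint in the MD phases: Day 57 (17.2.2). Last visit: Day 148 (8.1.2, 8.1.3).
- Days 58 to 148: 148 − 57 = 91 days; 91/148 = 61% of trial days.
- This is calendar time, not withdrawal risk.

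**Step 2: one subject who withdraws consent on Day 100, section by section.**

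| Section | Consequence |
|---|---|
| 6.4 | Withdrawing consent is a listed withdrawal criterion |
| 16 | A withdrawal criterion was met during the trial, so not in PP |
| 16 | Randomised and exposed, so in ITT with the Day 57 value |
| 18.2 | Data used in the per protocol/intention to treat population |

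Under 6.4 and 16 no consent withdrawal can ever be in PP, whatever the day. The reference to PP in 18.2 is therefore either contradictory or without effect.

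**Step 3: sensitivity of a 26+13 comparison.** The responder counts and the losses are assumed, since the protocol gives no withdrawal rate after Day 57. Only non-responders are removed, all after Day 57. P-values are two-sided Fisher.

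| Removed after Day 57 | Active | Placebo | Difference | p |
|---|---|---|---|---|
| none | 13/26 (50%) | 2/13 (15%) | 35 points | 0.045 |
| 2 placebo | 13/26 (50%) | 2/11 (18%) | 32 points | 0.14 |
| 4 active | 13/22 (59%) | 2/13 (15%) | 44 points | 0.016 |
| 4 active and 2 placebo | 13/22 (59%) | 2/11 (18%) | 41 points | 0.034 |

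No Day 57 value differs between rows. Placebo losses shrink the apparent effect and active losses enlarge it.

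**Step 4: the same check near the design rates.** 60% of 26 is 15.6 and 10% of 13 is 1.3, so take 16/26 v 1/13: p=0.0018. Removing 2 placebo non-responders gives 16/26 v 1/11, p=0.004; removing 4 gives 16/26 v 1/9, p=0.018. With an effect of that size the PP result stays below 5% in both cases.

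**Step 5: the SD phase.** Section 17.2.2 places PASI75 at Day 29. The post-dose visit lists in 8.1.1 name PASI after dosing (Day 1 to Day 2), at Days 15, 57 and 85, and at the last visit on Day 106, but not at Day 29. The SD flow chart rows are not legible in the text at hand and could not be used to check this. The time-limit defect is the same in the SD phase, but there is no settled visit to tie the condition to.

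**The case against.** The strongest reply is that little depends on the PP set. ITT is the efficacy set, a Day 100 withdrawal stays in it with the Day 57 value, and no sample size or decision rule uses PP. All of that stands and limits the weight of the point. It does not follow that the matter can be left to a SAP: the protocol already states a rule, and followed as written that rule conditions on events after the endpoint.

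On 18.2, the slash may simply mean whichever set applies, since the passage is about keeping data already collected. That is a fair reading, but the protocol does not say so. A reader might infer that PP membership cannot be settled at all. That goes too far: section 16 is where the sets are defined, and it requires exclusions to be documented and signed before database release. That review sets no cut-off, however.

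A reader might also infer that later leavers would be mostly placebo subjects. The documents do not support this. In the illustration there are 13 − 2 = 11 placebo and 26 − 13 = 13 active non-responders, so if non-response drives leaving, both arms would lose subjects. Nor do the p-values predict harm: the starting table is borderline, the placebo-only loss works against the drug, and Step 4 shows a result that survives.

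**Conclusion.** The point holds as a correctable flaw in the definition of a supportive analysis set. The PP condition in section 16 runs past the PASI75 endpoint by 91 days in the MD phases and counts events that are uninformative about adherence up to Day 57, including sponsor closure. Section 18.2 does not fit with sections 16 and 6.4 on consent withdrawals and needs reconciling.

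Size and direction are unknown, because no withdrawal rate after Day 57 is given. Under the assumed losses in Step 3, the PP p-value ranges from 0.016 to 0.14 around an unchanged full-set value of 0.045. The tempting stronger conclusion, that the efficacy result is biased or that the bias favours the drug, is not supported: the ITT efficacy analysis is untouched, and the PP shift can go either way. The change is still worth making because it removes an avoidable selection on post-endpoint events at almost no cost.

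**What to change.** 1. **Section 16.** For the PP efficacy analysis, require ITT membership, all inclusion and no exclusion criteria at entry, and no withdrawal criterion met before completion of the endpoint assessment (Day 57 in the MD phases). State that sponsor closure after that assessment is not a reason for exclusion.
2. **Section 18.2.** State that data collected before consent withdrawal are used in ITT, and in PP only if the section 16 definition is met.
3. **SD phase.** Reconcile the Day 29 PASI75 time point in 17.2.2 with the visit list in 8.1.1, then apply the same principle to the agreed visit.

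Items 1 and 2 are wording changes that need no further subjects, visits or data and leave the withdrawal rules for subjects as they are. Item 3 first requires the sponsor to settle which SD visit carries the PASI75 assessment.

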## 17 Statistical considerations

It is not acceptable that anyone, Investigator nor sponsor, makes any form of statistical comparisons between treatment groups before database release.

Novo Nordisk A/S will be responsible for the statistical analysis.

### 17.1 Sample size calculation

No formal power calculation has been performed in connection with the SD dose-escalation and MD dose-escalation phases. The number of subjects dosed within each cohort is based on safety. The objective is to expose the lowest possible number of subjects to the investigational drug, while still being able to assess safety, PK and PD data. Placebo will be used in order to distinguish between drug related effects and non-drug related effects.

The sample size calculation for the expansion cohort is based on an assumption of 60% of the Anti-IL-20 (109-0012) 100 mg/vial treated subjects and 10% of the placebo treated subjects, respectively, reaching a 75% reduction in PASI (PASI75), when comparing PASI, measured two weeks after last (fourth) dosing in the MD expansion phase, to baseline value measured prior to the first dose. Basing the comparison between the two treatment groups on a two sided Fisher's exact test, a 5 % significance level, and a 2:1 allocation ratio between Anti-IL-20 (109-0012) 100 mg/vial and placebo, including 26 subjects in the Anti-IL-20 (109-0012) 100 mg/vial group and 13 subjects in the placebo group should result in a power of 83%. Some additional sample size calculation using alternative assumptions are included in [Table 17-1](#).

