#### MD expansion phase

- The primary endpoint for efficacy is PASI (PASI75).

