### 8.3 Assessments for efficacy

Efficacy is a secondary endpoint for the SD and MD dose-escalation phases. In the MD expansion cohort, efficacy will be a primary endpoint, evaluated by PASI, PGA and VAS.

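### Section 17.1 powers the expansion phase on a Fisher test of PASI75, but Section 17.2 only summarises PASI75 and Section 8.3 names a different set of primary endpoints

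*Protocol*

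**What the plan says.** - **Endpoint.** Section 4.2, for the MD expansion phase: "The primary endpoint for efficacy is PASI (PASI75" (the closing bracket is cut from the quote). The same section lists PGA, VAS and quality of life as secondary efficacy endpoints.
- **Sizing.** Section 17.1 is "based on an assumption of 60% of the Anti-IL-20 (109-0012) 100 mg/vial treated subjects and 10% of the placebo treated subjects" reaching PASI75 two weeks after the fourth dose. It continues "Basing the comparison between the two treatment groups on a two sided Fisher's exact test", with "a 5 % significance level, and a 2:1 allocation ratio between Anti-IL-20 (109-0012) 100 mg/vial and placebo", and concludes that 26 active and "13 subjects in the placebo group should result in a power of 83" per cent. It does not say how the two-sided p-value is formed. Table 17-1 gives four alternative scenarios and repeats this one.
- **Methods.** Section 17.2.1, headed Primary endpoint, describes adverse events only, by descriptive statistics. PASI75 appears in 17.2.2 under secondary endpoints, with a bracketed note that it is primary for the expansion phase. Its stated treatment is "PASI75 and PASI90 will be summarised by trial phase and dose". No test, effect estimate or interval is named there.
- **Assessments.** Section 8.3: "In the MD expansion cohort, efficacy will be a primary endpoint, evaluated by PASI, PGA and VAS".

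**The concern.** The expansion phase is where the protocol seeks proof of principle, and its 39 subjects were chosen to give a hypothesis test a stated power. A reader who goes to the methods section for that test finds a safety paragraph under the primary heading and a descriptive summary of the powered endpoint. A reader who goes to 8.3 finds three primary measures where 4.2 has one.

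Two things are at stake. First, which result decides the phase should be fixed in one place before its data are seen, particularly as the dose-escalation data will already have been unblinded for the decision to start it. Second, two-sided Fisher p-values are formed in more than one way. With 13 placebo subjects the choice can move a result across 5%, so the version used for sizing ought to be the version used for analysis.

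**Working it through.** **Inputs.** Section 17.1: p1 = 0.60, p0 = 0.10, n1 = 26, n0 = 13, two-sided 5%, stated power 83%. Table 17-1: four further scenarios.

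**Method.** Enumerate all 27 × 14 = 378 outcomes (x, y). Power is the sum, over outcomes with p ≤ 0.05, of Bin(x; 26, 0.60) × Bin(y; 13, 0.10). With m = x + y responders in total, Fisher's p comes from the hypergeometric distribution of x given m. There are two common two-sided versions:

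- doubled tail: p = 2 × the smaller one-sided tail;
- minimum likelihood: p = the sum of the probabilities of all tables no more likely than the one observed.

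**Step 1: reproduce the plan's figures (power, %).**

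| Scenario | Stated | Doubled tail | Minimum likelihood |
|---|---|---|---|
| 60 v 15, 32+16 | 80 | 81.3 | 83.8 |
| 55 v 10, 30+15 | 80 | 81.8 | 85.0 |
| 70 v 20, 28+14 | 80 | 82.0 | 87.7 |
| 70 v 10, 22+11 | 90 | 90.3 | 92.4 |
| 60 v 10, 26+13 | 83 | 83.8 | 89.0 |

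The doubled tail is within about 2 points of the stated figure in every column and the other version is farther off in every column. The sizing evidently used the doubled tail.

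**Step 2: how often the choice matters.** At 26+13 every outcome rejected by the doubled tail is also rejected by minimum likelihood. The probability of disagreement is therefore the difference in power: 89.01 − 83.77 = 5.24, about 5%. The verdicts split at one active count for each placebo count from 0 to 4.

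Example, 11/26 v 1/13 (m = 12):

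- Upper tail: P(11) + P(12) = 0.02568 + 0.00247 = 0.02815.
- Doubled: 2 × 0.02815 = 0.056, not significant.
- Minimum likelihood adds the lower-tail tables no more likely than 0.02568, which are P(4) + P(3) + P(2) = 0.00492 + 0.00048 + 0.00002 = 0.00542. This gives 0.02815 + 0.00542 = 0.034, significant.

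Likewise 13/26 v 2/13 gives 0.075 (doubled) or 0.045 (minimum likelihood).

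**Step 3: an exact unconditional alternative at 26+13.** Boschloo's test takes a Fisher p-value as its ordering statistic and sets the cut-off so that the size, maximised over a common response rate, is at most 5%.

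| Test | Power, 60 v 10 (%) | Maximum size (%) |
|---|---|---|
| Fisher, doubled tail | 83.8 | 2.2 |
| Fisher, minimum likelihood | 89.0 | 3.4 |
| Boschloo, ordered by doubled Fisher p | 90.6 | 4.5 |
| Boschloo, ordered by minimum-likelihood Fisher p | 91.0 | 4.7 |

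The gain is 90.6 − 83.8 = 6.8 to 91.0 − 83.8 = 7.2 points over the doubled tail, and 90.6 − 89.0 = 1.6 to 91.0 − 89.0 = 2.0 points over minimum likelihood. With a 15% placebo rate (a rate used in Table 17-1) at 26+13, the powers are 70.0% (doubled), 77.4% (minimum likelihood) and 80.7% (Boschloo, minimum-likelihood ordering).

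**Step 4: the sections side by side.**

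| Section | Role of PASI75 in the expansion phase | Analysis given |
|---|---|---|
| 4.2 | only primary; PGA and VAS secondary | none |
| 8.3 | primary together with PGA and VAS | none |
| 17.1 | endpoint powered | two-sided Fisher, 5% |
| 17.2.1 | absent | adverse events, descriptive |
| 17.2.2 | under secondary, noted as primary | summary only |

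**The case against.** The strongest reply is that little is actually missing. Section 17.1 names the comparison, test, level and sidedness. Section 17.2.2 marks PASI75 as primary for this phase and fixes Day 57 against baseline. Section 16 assigns efficacy to the ITT set. The p-value version is detail that an analysis plan, not shown here, may hold, and 26+13 reaches at least 83.8% power under either version. Section 8.3 echoes the wider efficacy objective in 4.1, while the endpoint section, 4.2, is clear. Most of this stands, and it limits the point to consistency. It does not remove the conflict: the methods section gives the powered endpoint a descriptive treatment, and 8.3 contradicts 4.2.

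Three stronger readings are tempting, and the documents do not support them.

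- A reader might infer that 83% is miscalculated, because software using minimum likelihood returns 89.0%. It is correct for the doubled tail.
- A reader might infer that three primary endpoints inflate the false-positive rate. No section plans a test of PGA or VAS, and PASI and PGA grade the same skin signs, so a calculation treating the endpoints as independent tests would not describe this plan.
- A reader might infer that choosing Fisher is a defect. It is valid at 5%, and an unconditional test is an efficiency option. The gain also depends on the test: Barnard's pooled-Z version gives 89.1%, practically the same as minimum-likelihood Fisher.

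**Conclusion.** The point holds as an inconsistency. The comparison that justifies 39 subjects stands in 17.1 but not in 17.2, and 8.3 disagrees with 4.2 on what is primary. The sample size and the stated 83% are sound.

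The unstated p-value version has a measurable but modest effect: 5.2 points of power, and an equal probability that the two versions disagree, under 60% v 10% with 26+13 analysed. The 5.2 points depend on those rates; that the versions split at particular outcomes does not. The inference that the doubled tail was used rests on agreement with all five columns of Table 17-1, not on a statement in the text.

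**What to change.** 1. **Section 17.2.** Add a primary efficacy paragraph for the expansion phase: active against placebo on PASI75 at Day 57, ITT set, two-sided 5%, one fully specified test, and an exact confidence interval for the difference in proportions.
2. **Choice of test.** Preferably Boschloo's test with its ordering statistic written down, since the ordering changes the rejection region: minimum-likelihood Fisher p (power 91.0%, maximum size 4.7%) or doubled Fisher p (90.6%, 4.5%). If Fisher is kept, state the version and its power: doubled tail 83.8%, or minimum likelihood 89.0%.
3. **Section 17.1.** Restate the power for the test chosen.
4. **Section 8.3.** Name PASI75 as the only primary endpoint of the expansion phase, with PGA and VAS secondary as in 4.2.

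The cost is wording in the protocol, carried into any analysis plan. The sample size and visits do not change. Boschloo's test is less familiar to readers than Fisher's, which is a small price for the added power.
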